#### Numerical parameters

3.4.3

Machine learning algorithms and statistical techniques will be used to analyze numerical data. The optimal technique will be selected based on the characteristics of the data. Although not a priority, some basic classical classifiers, including support vector machines [SVM], k-nearest neighbors [KNN], and ensemble methods, along with statistical analyses, will be included for comparative analysis. In such cases, feature extraction from the dataset is important. For this purpose, the RMSSD, LF, HF, LF/HF, SDNN, SCL, SCR, HbO, HbR, and Oxy parameters will be used as features.

### Assessing the results

3.5

The analysis and evaluation of the data obtained from the collected stress and anxiety tests will be performed by the researcher physician. The supervisor and researchers will analyze and evaluate the respiratory rate and ECG, PCG, EDR, and fNIRS data. Respiratory rate, ECG, PCG, EDR, and fNIRS data will be analyzed and evaluated by the supervisor and researchers.

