Study type	Allocation: non-randomized Intervention model: parallel assignment Primary purpose: treatment
Date of first enrollment	December, 2024.
Target sample size	36
Recruitment status	Recruiting.
Primary outcome(s)	Method of measurement: Biopotentials (ECG, PCG, EDA, fNIRS, respiratory rhythm) Timepoint: pre-treatment, post-treatment, and follow-up.
Key secondary outcomes	Changes in neuroimaging measures Timepoint: pre-treatment, post-treatment, and follow-up. Changes in biopotential measures Timepoint: pre-treatment, post-treatment, and follow-up.
Ethics Review	This project received ethical approval from Harran University with the decision of the clinical research ethics committee on 03 July 2024.
Completion Date	October, 2025

The SPIRIT reporting guidelines recommend these items to be included in trial protocols to provide a brief, structured overview of a trial.

Our study is a non-randomized, parallel-group cohort study. Patients were assigned to a group in the chronological order of enrollment in the study. Therefore, consecutive sampling was used for allocation concealment. The inclusion and exclusion criteria will be applied uniformly to all patients, regardless of group, without exception. At inclusion, baseline characteristics will be compared between groups, including age, sex, and whether participants experienced the earthquake as a traumatic event. The comparability of the groups at inclusion will be verified by ensuring that there are no significant differences between groups.

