#### Statistical methods

3.5.1

RMSSD, HF, and LF derived from HRV will be the primary pilot outcomes for estimating the effect size and variance, with a view to calculating the sample size for a future confirmatory trial. The primary outcomes will be assessed at the final session and compared with those obtained at the first session. The analyses will be conducted using a linear mixed-model (LMM), with group and time as fixed effects or using an analysis of covariance (ANCOVA). Other measures, such as electrodermal activity, respiratory rate, and neuroimaging, will be treated as secondary endpoints for exploratory purposes.

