## Limitations

5

Although the ALLOSTAT0001 project provides a great deal of new information, it is associated with several limitations for which mitigation strategies can be proposed. The risks are detailed as follows.

Many young participants from the city where the earthquake occurred are studying in another city. This may limit our ability to recruit participants who survived the disaster, restricting the sample size to no more than 36 participants. We expect to recruit the number of participants needed to reach statistical significance in this study. For the study using deep learning techniques, 36 participants are expected to be sufficient when using transfer learning.

At the end of the project, missing data may occur. When collecting signals, we may notice that the signal is incomplete or has anomalies. As missing data can limit statistical comparisons between groups, we will reduce this problem by recruiting other participants. We will recruit an additional 10 participants who will provide backup data. If we cannot recruit participants aged 20–25 years because many students were absent (at the end of their school holidays) during the earthquake in 2023, we can extend the age range to 18–25 years. In addition, we will take the necessary steps in the statistical analysis plan to address the missing data.

Each participant will be invited to return 4 weeks after the final session for a follow-up evaluation. However, the start of holiday period may make it challenging to collect data after the event. We will take care to plan the sessions and the day of the follow-up evaluation, prioritizing participants who will be staying in the city during the holiday period.

This study is a preliminary investigation aimed at exploring whether real time, closed-loop phonocardiogram stimulation enables individuals to manage acute stress more effectively and whether the effects of this treatment persist for up to 4 weeks. The design of a further, longer-term, and more comprehensive study will help to substantiate claims regarding long-term cardiovascular or psychological outcomes.

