This study did not include an acoustically equivalent sham arm (scrambled sound), thus limiting the ability to completely isolate the specific effects of real-time heart sounds from the non-specific effects of listening and directed attention. However, the comparison between the silent, metronome, and heart-sound arms provided a partial separation of these effects. The main objective of this study is to explore the overall efficacy of the intervention under real-world conditions rather than to isolate its precise mechanism of action. Future studies incorporating an acoustically matched sham arm are necessary to confirm the specificity of the proposed mechanism.

Another limitation is that the first session, the subsequent 10 sessions, and the day of the follow-up evaluation for all groups may not be conducted in the same season. As seasons are known to affect physiological parameters (Goswami et al., 2021; Goswami et al., 2020; Trozic et al., 2020), we will endeavor to conduct most recordings during a single season. This should prevent differences in ECG signals owing to seasonal changes.

Because of the front-end morphology of each participant, during measurements with fNIRS, not all 16 channels can produce significant signals. We will, therefore, use the maximum number of active channels for all participants. We will use a headband or cap to improve contact with the prefrontal area for all participants. At worst, 12 channels will provide sufficient information about the right, central, and left prefrontal cortex activity.

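### Section 3.5 states no masking to arm or session for the study staff who evaluate the ECG signals, so arm-dependent processing of the primary RMSSD, HF and LF outcomes cannot be excluded

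*Protocol article*

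**What the plan says.** Section 3.5 (Assessing the results) names the evaluators. For the physiological signals: "The supervisor and researchers will analyze and evaluate the respiratory rate and ECG, PCG, EDR, and fNIRS data". For the questionnaires: "The analysis and evaluation of the data obtained from the collected stress and anxiety tests will be performed by the researcher physician". Neither sentence mentions coded files, a masked reader or the order of work, and no other part of the article mentions blinding or masking.

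Section 3.5.1 sets the primary outcomes: "RMSSD, HF, and LF derived from HRV will be the primary pilot outcomes for estimating the effect size and variance". The contrast is over time: "The primary outcomes will be assessed at the final session and compared with those obtained at the first session". The model is either a linear mixed model or ANCOVA. Electrodermal, respiratory and neuroimaging measures are secondary and exploratory.

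On design, Table 1 records "Allocation: non-randomized Intervention model: parallel assignment Primary purpose: treatment", and Section 3 says that participants enter groups in order of enrolment. In Section 3.1.2 the control group hears nothing and the other two groups hear heart sound or a metronome. Section 5 acknowledges that there is no acoustically matched sham.

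On signal quality, Section 5 says: "When collecting signals, we may notice that the signal is incomplete or has anomalies". Its response is to recruit other participants, with 10 extra as backup, and to leave missing-data handling to the statistical analysis plan. On fNIRS it says: "We will, therefore, use the maximum number of active channels for all participants".

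**The concern.** Silence and sound cannot be disguised from the participant or from whoever delivers the session. The stage at which masking remains possible is the processing of stored recordings. Section 3.5 describes that stage and includes no masking.

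RMSSD, HF and LF are all computed from the series of beat-to-beat intervals, so they depend on how missed, extra or ectopic beats and noisy stretches are handled. If those decisions, or decisions to replace a participant, were influenced by knowledge of arm or session, the group-by-time estimate would carry the influence. With 10 to 12 participants per group, few such decisions would be needed. The pilot exists to supply an effect size and variance for a later trial, so a distortion here would pass into that trial's sample size.

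**Working it through.** The plan gives no figure on this point, so there is none to reproduce. The check has two parts.

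**1. The text, step by step**

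- *Who evaluates:* the supervisor and researchers (Section 3.5). These are study staff; no independent reader is named.
- *Is arm recognisable?* During a session, yes: silent control (Section 3.1.2) and no matched sham (Section 5). From the files, possibly: allocation follows enrolment order (Section 3), so a participant number or recording date may point to the arm.
- *Are labels needed by the analysts at some stage?* Yes. Sections 3.4.1 and 3.4.2 plan classification of control against treatment and of before against after. Nothing says that labels are withheld until the signals have been cleaned.
- *Can a quality judgement change the data set?* Yes. Section 5 answers incomplete or anomalous signals by recruiting others. The 10 backups are 10/36 = 28% of the target of 36, or 10/30 = 33% of the minimum of 30.
- *What does the fNIRS channel statement affect?* Only exploratory outcomes (Section 3.5.1), not the primary ones.

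**2. Sensitivity of RMSSD to uncorrected artefact (illustration only)**

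Assumed inputs, none from the article: a 5-minute segment at 75 beats per minute, so 375 intervals of mean 800 ms; true RMSSD 40 ms.

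- *One missed beat.* Two intervals merge into one of about 1600 ms. This leaves 374 intervals and 373 successive differences, two of them near 800 ms. RMSSD ≈ √(40² + 2 × 800²/373) = √(1600 + 3432) ≈ 71 ms.
- *One beat 200 ms early with a compensating pause.* The added squares are 200² + 400² + 200² = 240,000 over 374 differences. RMSSD ≈ √(1600 + 642) ≈ 47 ms. Simulation gave 47.4 ms, and 59.3 ms for three such beats.
- *Other starting values, by simulation.* From a true 30 ms, one early beat gives 39.1 ms and three give 53.1 ms. From 50 ms, the figures are 56.1 and 66.5 ms.

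In one of 10 participants, the missed beat moves the arm mean by (71 − 40)/10 ≈ 3.1 ms and the early beat by (47 − 40)/10 ≈ 0.7 ms. No calculation was made for HF or LF.

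**What an arm-related bias would do if one existed.** Assume no true effect, a two-sample t test at two-sided 5%, and a bias expressed in SD units:

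| Assumed bias | Error rate, n = 10 per arm | Error rate, n = 12 per arm |
|---|---|---|
| 0.25 SD | 8.3% | 9.0% |
| 0.50 SD | 18.5% | 21.6% |
| 0.75 SD | 35.5% | 42.0% |

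These are conditional statements. The article gives no basis for choosing among the rows, or for ruling out zero.

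**The case against.** The strongest reply is that this is a finding of silence. Section 3.5 only names roles, and having study staff analyse data is ordinary. File coding and artefact rules can sit in a full protocol or analysis plan that is not shown. The ECG is recorded by an instrument, not rated by a person. Much of this stands. A reader might infer that the people who run the sessions also process the signals, that they do so knowing arm and session, and that beats will be edited by hand at their discretion. The article says none of these things, and the point does not rest on them.

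The reply also limits the supporting text. The fNIRS sentence cannot bear on the primary outcomes, and Section 5 attributes channel loss to participants' morphology, not to arm. The statement in Section 3.4.3 that "The optimal technique will be selected based on the characteristics of the data" concerns parameters already derived, so it is no evidence about signal processing.

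The arithmetic does not measure bias either. A missed beat is a detection error that a good artefact rule would catch, masked or not. Assuming a between-person RMSSD SD of 15 to 25 ms (none is given), the standard error of a two-arm difference at 10 per arm is SD × √(2/10) = 6.7 to 11.2 ms. A 3.1 ms shift is then 0.28 to 0.46 standard errors, and 0.7 ms is about 0.1 or less. In a non-randomised pilot without a sham, allocation may well be the larger threat.

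What does not stand is that the matter belongs wholly to the analysis plan. Section 5 defers only missing data to it. Who evaluates the signals is something that the article itself sets out, and its limitations section admits the missing sham but not the lack of stated masking.

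**Conclusion.** The point holds as a gap in safeguards. Study staff evaluate the signals behind RMSSD, HF and LF, no masking to arm or session is stated, the arms are recognisable, and a quality judgement can bring in replacement participants. Arm-dependent processing or replacement therefore cannot be excluded.

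It does not hold as a demonstration of bias. The direction and size of any effect cannot be determined from the document. The 47 and 71 ms figures rest on assumed inputs and show only that RMSSD reacts strongly to one or two badly handled beats. The error rates in the table depend on assumed biases for which the article offers no evidence. This is a worthwhile and inexpensive improvement, not a defect that invalidates the pilot.

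**What to change.** Amend Section 3.5 as follows:

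1. Before processing, give each stored ECG recording a random code that hides participant, arm and session. Remove recording dates and any stimulus markers, since enrolment order may reveal the arm. Do the same for EDA, respiration and fNIRS as secondary outcomes.
2. On coded files, under written rules common to all arms, complete R-peak and artefact correction, decisions to reject or replace a signal, and fNIRS channel acceptance.
3. Lock the derived parameters and the choice between linear mixed model and ANCOVA.
4. Only then join the key.

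No change is needed for the DASS-21, where coded scoring of participants' own answers would add little.

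Section 3 gives data collection as completed by 30 June 2025, and the article does not say how far processing has gone. Where it was done with labels visible, reprocess the ECG under code or list unmasked processing in Section 5.

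The cost is a renaming script, a short delay before labelled analysis, and a key-holder from the existing team who does not process signals. No extra visit or participant is needed. Whether the team can spare such a person is an assumption.

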#### Statistical methods

3.5.1

RMSSD, HF, and LF derived from HRV will be the primary pilot outcomes for estimating the effect size and variance, with a view to calculating the sample size for a future confirmatory trial. The primary outcomes will be assessed at the final session and compared with those obtained at the first session. The analyses will be conducted using a linear mixed-model (LMM), with group and time as fixed effects or using an analysis of covariance (ANCOVA). Other measures, such as electrodermal activity, respiratory rate, and neuroimaging, will be treated as secondary endpoints for exploratory purposes.

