## Methods/design

3

The Project has received ethics approval from Harran University with the decision of the clinical research ethics committee. The study was registered under the number E-76244175-050.04-346993, on the 10th of June 2024. The study will be conducted at Kahramanmaras Sütçü İmam University in Türkiye. The study was subsequently registered with www.ClinicalTrials.gov under the registration number NCT06919055 in March 2025 and follows the Standard Protocol Items: Recommendations for Interventional Trials (SPIRIT) reporting guidelines (Chan et al., 2013). All items from the World Health Organization Trial Registration Data Set are summarized in Table 1 according to the SPIRIT reporting guidelines. Data collection began in December 2024 and completed by 30 June 2025.

**Table 1 tab1:** Items from the World Health Organization trial registration dataset.

Section/item	Information
Primary Registry and Trial Identifying Number	ClinicalTrials.gov, NCT06919055
Date of registration in primary registry	17 March, 2025.
Secondary identifying numbers	124S102
Source(s) of monetary or material support	The Scientific and Technological Research Council of Türkiye (TÜBİTAK)
Primary Sponsor	[name] and [name]
Secondary sponsor (s)	[name], [name]
Contact for public queries	[name], [contact]
Contact for scientific queries	[name], [contact] and [name] [contact]
Public title	Allostat0001
Scientific title	Biofeedback with Heart Sound Following Trauma
Countries of recruitment	Turkey
Health condition(s) or problem(s) studied	This study aims to examine how individuals cope with trauma-related situations using a biofeedback method, which could be developed to manage stress-related coping.
Intervention(s)	1. Control 2. Heart sound stimulation 3. Metronome with ECG rate stimulation
Key inclusion and exclusion criteria	36 earthquake survivor university students aged between 20 and 25 years will participate in the experiment. Participants will be healthy, non-obese men (*n* = 18) and women (*n* = 18). In particular, all participants should have experienced an earthquake disaster in the local region. All participants should be free of any chronic or acute infection, neurological, psychiatric, and/or cardiovascular disease. They must be non-smokers, have no alcohol or drug addiction, and not be under any medical treatment. Pregnant or breastfeeding women will not be included in the study.

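### Table 1 and section 3.5.1 define the primary outcome differently, in measures and in time points, and the article does not settle whether the primaries are to be estimated or tested

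*Protocol article*

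**What the plan says.** The article defines the primary outcome twice.

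- **Section 3, Table 1.** The text introduces the table with "All items from the World Health Organization Trial Registration Data Set are summarized in Table 1". The primary entry reads "Method of measurement: Biopotentials (ECG, PCG, EDA, fNIRS, respiratory rhythm) Timepoint: pre-treatment, post-treatment, and follow-up". It names no parameter within any signal. The key secondary entries are "Changes in neuroimaging measures Timepoint: pre-treatment, post-treatment, and follow-up" and "Changes in biopotential measures Timepoint: pre-treatment, post-treatment, and follow-up".
- **Section 3.5.1.** "RMSSD, HF, and LF derived from HRV will be the primary pilot outcomes for estimating the effect size and variance", with a later confirmatory trial in view. On timing: "The primary outcomes will be assessed at the final session and compared with those obtained at the first session". On the rest: "Other measures, such as electrodermal activity, respiratory rate, and neuroimaging, will be treated as secondary endpoints for exploratory purposes". The model is a linear mixed model or ANCOVA. The three outcomes are not ranked, no contrast among the three arms is singled out, and no significance level is given.

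On purpose, section 5 (Limitations) calls the study preliminary but also expects enough participants to reach statistical significance. Section 3.4.2 wants classification to show that group differences are significant, and section 4 makes wider use of the protocol depend on significant results.

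On dates, section 3 puts the start of data collection in December 2024, registration on 17 March 2025 and the end of collection at 30 June 2025. The article does not say when the 3.5.1 primaries were chosen.

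**The concern.** A primary outcome tells the reader in advance which result carries the study's conclusion. Here a favourable EDA, respiration or fNIRS result could be reported as primary by citing Table 1, or an unfavourable one set aside as exploratory by citing 3.5.1. The same holds for a result at the 4-week follow-up. Table 1 also conflicts with itself, because biopotentials are both primary and secondary, and fNIRS is primary while neuroimaging is secondary.

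The second issue is purpose. If RMSSD, HF and LF are only estimated, three unranked outcomes over three arms are acceptable as long as all are reported. If they are tested, as section 5 implies, the number of ways to obtain a nominally significant result matters. Selecting the most favourable estimate would also bias upward the effect size that the pilot is meant to supply.

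**Working it through.** **1. The two definitions side by side**

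| Item | Table 1 | Section 3.5.1 |
|---|---|---|
| RMSSD, HF, LF | Not named; covered by ECG as primary and by biopotentials as secondary | Primary |
| PCG | Primary, and again secondary as a biopotential | Not named |
| EDA | Primary, and again secondary as a biopotential | Secondary, exploratory |
| Respiration | Primary, and again secondary as a biopotential | Secondary, exploratory |
| fNIRS | Primary, and again secondary as neuroimaging | Secondary, exploratory |
| Time points | Before treatment, after treatment and follow-up | Final session versus first session |

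The two columns cannot both hold for EDA, respiration, fNIRS or follow-up.

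**2. Inputs for the error rate**

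- Arms: 3 (Table 1). Primary outcomes: 3 (section 3.5.1).
- Participants per arm: 10-12 (section 3.1.1). The stated totals follow: 3 × 12 = 36 and 3 × 10 = 30. The article gives no power or alpha figure to reproduce.
- Assumed: two-sided 0.05 per test, and a common correlation among the three outcomes between 0 and 0.9.

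**3. Number of tests under three readings**

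- One omnibus test of the arms per outcome: 3 × 1 = 3.
- Each active arm versus control: 3 × 2 = 6.
- All pairs of arms: 3 × 3 = 9.

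**4. Chance of at least one false positive when nothing works**

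For independent tests, 1 − 0.95^k:

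- k = 3: 1 − 0.95^3 = 14.3%
- k = 6: 1 − 0.95^6 = 26.5%
- k = 9: 1 − 0.95^9 = 37.0%

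Contrasts share arms and the outcomes are correlated, so the independent figures are upper values. A simulation of 20,000 null trials per setting (10 or 12 per arm, variance pooled over the three arms, correlation 0 to 0.9) gave:

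- omnibus: 8.7% to 14.4%
- six contrasts: 15.1% to 24.7%
- nine contrasts: 19.5% to 31.9%

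The low ends belong to correlation 0.9 and the high ends to correlation 0. Taking both methods together, the ranges are about 9-14%, 15-26% and 20-37%. One outcome with one contrast would give 5%.

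**5. What estimation can deliver**

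The approximate 95% half-width for a standardised difference between two arms is 1.96 × √(2/n): 0.88 at n = 10 and 0.80 at n = 12. The difference detectable with 80% power at an unadjusted 0.05 is (1.96 + 0.84) × √(2/n): 1.25 and 1.14. Only very large effects would be likely to reach significance.

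**The case against.** The strongest reply is that section 3.5.1 describes a pilot. It estimates effect size and variance and states no hypothesis test, alpha or success rule. Estimating three parameters needs no familywise control. The counts of six and nine are readings of the plan; a mixed model or ANCOVA could be summarised by one omnibus test per outcome, at 9-14%. All of this stands, so the error rates apply only if significance is claimed. Sections 3.4.2, 4 and 5 show that such claims are anticipated, although 3.4.2 concerns classification and not the HRV outcomes.

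A reader might infer several stronger points that the document does not support:

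- *That the primary label protects nothing.* Section 3.5.1 narrows five signal types to three named parameters and one before-after comparison.
- *That the primaries were changed after the data were seen.* The choice is undated, so this can be neither shown nor excluded.
- *That a missing multiplicity rule is itself an error.* Such a rule may stand in the statistical analysis plan, which is not shown.
- *That LF does not belong because section 3.3 leaves it out of its list of vagal indices.* HF is also outside that list, and the aims concern autonomic stability more broadly.
- *That the registry entry is wrong.* Only Table 1's summary of it can be read here.

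**Conclusion.** The contradiction holds on the face of the article and needs no assumption: two incompatible primary-outcome definitions, differing in measures and time points, with Table 1 also duplicating primary items as secondary. It should be resolved before any result is presented as primary.

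The multiplicity concern holds conditionally. With three unranked primaries, three arms and an assumed 0.05 per test, the chance of at least one false positive is about 9-14%, 15-26% or 20-37%, depending on whether three, six or nine tests are made and on the correlation among outcomes. If the primaries are reported purely as estimates, no adjustment is needed and this part falls away. The article does not settle which applies, because 3.5.1 says estimation and section 5 expects significance.

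**What to change.** - Align Table 1 with section 3.5.1: RMSSD, HF and LF primary, final versus first session; EDA, respiration, neuroimaging and follow-up secondary and exploratory. Delete the duplicate biopotential entry. Amend the registry entry if it reads as Table 1 does.
- State the date on which the 3.5.1 primaries were fixed, and whether anyone had access to outcome data by then.
- Report RMSSD, HF and LF for every arm contrast as estimates with confidence intervals and no significance claim.
- Remove or reword the sentence in section 5 that expects statistical significance.
- Name a single primary outcome and contrast (for example RMSSD, real-time PCG versus control) only if it can be shown to have been fixed before data access. Collection is stated to have ended by 30 June 2025, so a choice made now would itself be selection after the data and should be labelled post hoc.

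The cost is wording only. The study gives up significance claims on the primaries, which its stated pilot purpose does not need.
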